#### Measurement of uterine tone

The obstetrician provides an assessment of the uterine tone by manual palpation using a LAS ranging from 0 to 100. Manual palpation of the uterus is the standard used to assess uterine tone in daily clinical practice.

#### Haemodynamic measurements

Blood pressure is measured non-invasively using a cuff on the upper arm. All haemodynamic data (including ST segment alterations) are recorded and stored in the anaesthesia monitor (IntelliVue MX800, Philips AG Healthcare, Zurich, Switzerland). The programme ixTrend from ixellence (ixellence GmbH, Wildau, Germany) is used to ensure direct transfer from the monitor to the study computer.

### Statistics

#### Sample size justification

To be 80 % sure that the lower limit of a one-sided 97.5 % confidence interval (CI) will be above the non-inferiority limit of −10 points on the LAS, 63 patients per group are required assuming a standard deviation (SD) of 20. Offsetting a maximal dropout of 10 %, this leads to a total sample size of 140 patients. The non-inferiority margin has been defined to be −10 on the LAS by the four most senior obstetricians at our institution. The SD had been derived from the results of a trial by Butwick et al., who used the same scale to assess the uterine tone [11].

#### Data management

All data from patients will be stored anonymously. Each patient will be assigned a unique patient-identity (ID) consisting of a three-digit number. The patient’s ID, name and date of birth will be stored separately in a different file in order to be able to examine queries in case of implausible values (reversible anonymisation). Only members of the study team have access to the data.

An electronic database featuring web-based access and using a secure (Secure Sockets Layer: SSL) connection is used for data entry. The database is password-protected and all data are encrypted. A consistency check is performed by logical data testing on the browser and on a random sample of 5 % by an independent study member.

#### Statistical analysis plan

The following baseline characteristics will be used to investigate comparability of both trial arms: age, body mass index, parity, gravidity, gestational week, risk factors for PPH, number of previous CS, planned or unplanned CS, reason for CS, experience level of the obstetrician, batch number. Continuous variables will be described by using the mean (SD) or median (interquartile range) as appropriate, categorical variables by using count (percentage).

In order to answer the primary research question, a CI of the mean difference in LAS score of the maximal uterine tone within the first 5 minutes after cord clamping will be calculated. If the lower limit of this CI does not include the pre-specified non-inferiority limit of −10, an inferiority of a short-infusion of more than 10 points on the LAS as compared to a bolus application is unlikely. In order to improve efficiency, an additional model will be built adjusting for the most relevant confounders, such as experience of the obstetrician, parity or number of previous CS, number of risk factors for PPH (multiple pregnancy, abnormal placentation, history of PPH or uterine atony), duration of surgery, and duration of antenatal oxytocin infusion. In order to compare the change of the uterine tone over time between both study groups, a generalised estimation equation (GEE) [17] will be built using an exchangeable correlation matrix (with an interaction term between treatment group and time). Moreover, the uterine tone over time will be displayed graphically.

The haemodynamic secondary outcomes (lowest mean arterial blood pressure and highest heart rate within the first 5 minutes after the administration of the study drug) will be analysed using a linear regression model adjusting for the corresponding baseline value and the amount of vasoactive drug administered during this period. In a further analysis, the course over time of mean arterial pressure and heart rate will be modelled using a GEE model with an exchangeable correlation matrix, using a knot at the average time of the lowest mean arterial pressure adjusted for the dosage of vasopressors administered, in order to compare the trend over time in both groups. Moreover, the change over time in blood pressure and heart rate will be displayed graphically. The incidence of any clinically relevant ST segment changes in both groups will be compared using a chi-squared or a Fisher’s exact test as appropriate. Further secondary endpoints will only be analysed descriptively. The comparison of the calculated blood loss will be adjusted in a linear regression model for whether or not the mother is breastfeeding.

All analyses and graphs will be performed using Intercooled Stata Version 13.1 for Mac (StataCorp, College Station, TX, USA). We will follow the Consolidated Standards of Reporting Trials (CONSORT) statement and its extension for non-inferiority trials for the future report [18, 19].

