### Randomisation and blinding

Randomisation for a 1:1 allocation of the study treatment is provided through an online-randomiser to ensure allocation concealment. This online-randomiser was integrated into the password-protected database. The randomisation took place immediately before the CS after having controlled the inclusion and exclusion criteria. The randomisation list was generated in Intercooled Stata Version 13.1 (StataCorp, College Station, TX, USA) using variable block sizes between 2 and 8. The list is safely stored in a separate and sealed file, which will only be opened if unblinding becomes necessary. This is considered to be unlikely since the concomitant treatment in case of insufficient uterine tone is independent of the mode of administration of carbetocin.

Subjects are randomised on arrival in the operating theatre to minimise the risk of dropouts after randomisation. To achieve similar numbers, randomisation is stratified for planned or unplanned CS (Fig. 1).

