### Choice of study population

This trial will include patients undergoing a planned and an unplanned CS. Patients undergoing a unplanned CS often have already received oxytocin to induce or enhance labour, thus, showing a different response to the intraoperative dosage of carbetocin. Therefore, we are using a stratified randomisation for planned and unplanned CS. Excluding these patients would limit the generalisability of our study results.

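### The primary non-inferiority CI leaves out the planned/unplanned stratum used in randomisation; adding it would be a free gain in precision if the stratum is prognostic

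*Protocol article*

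**What the plan says.** Under *Randomisation and blinding*, the protocol article states that "randomisation is stratified for planned or unplanned CS". Under *Choice of study population* it gives the reason: women with an unplanned caesarean have often had oxytocin already, thus "showing a different response to the intraoperative dosage of carbetocin".

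Under *Statistical analysis plan*, the primary question is answered by "a CI of the mean difference in LAS score of the maximal uterine tone" within 5 minutes of cord clamping, and the lower limit is judged against −10. No covariate is attached to this interval. Adjustment is placed in an additional model meant to improve efficiency. Its examples are obstetrician experience, parity or previous caesareans, number of haemorrhage risk factors, duration of surgery and duration of antenatal oxytocin. Planned versus unplanned caesarean is not among them. It is also not named for the GEE models, the haemodynamic regressions or the blood-loss regression. In the analysis section it appears only in the list of baseline characteristics.

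**The concern.** Blocked randomisation within strata balances the arms on planned/unplanned caesarean. Differences in mean tone between the strata therefore hardly contribute to the true sampling variance of the treatment difference. The ordinary two-sample standard error does not use this: it still counts the between-stratum spread as noise. If the stratum is prognostic, the interval is wider than the design warrants.

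The article gives some reason to expect a prognostic stratum. Every participant receives carbetocin by one route or the other, so a different response to carbetocin in unplanned cases would show up as a different mean tone in both arms.

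The verdict of the trial rests on one confidence limit against −10, and it must be met in both the intention-to-treat and the per-protocol analysis (section *Definition of dataset analysed*). The article itself looks for efficiency from covariates, but only in a model that does not decide the result.

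**Working it through.** **Inputs from the section *Sample size justification*:** margin −10 ("non-inferiority limit of −10 points on the LAS"), SD 20 ("assuming a standard deviation (SD) of 20"), one-sided 2.5% error, 80% power, "63 patients per group are required", 10% dropout. A true difference of 0 is not stated but reproduces the plan's figure.

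**The plan's own figure.** n per group = 2 × 20² × (1.96 + 0.8416)² / 10² = 62.8, so 63. Total = 126 / 0.9 = 140. Both match the article, with no allowance for adjustment.

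**Unadjusted baseline.** SE = 20 × √(2/63) = 3.563. The 95% half-width is 1.96 × 3.563 = 6.98. Power = Φ(10/3.563 − 1.96) = Φ(0.846) = 80.1% (79.5% from the noncentral t).

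**Effect of the stratum.** Let R² be the share of the total variance (20²) explained by planned/unplanned, and k = √(1 − R²). The article gives no value, so 5%, 10% and 20% are assumptions. Under stratified randomisation the true SE of the difference is 3.563 × k whichever analysis is used. The unadjusted analysis reports 3.563; the adjusted one reports 3.563 × k. Hence:

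- excess width of the unadjusted interval = 1/k − 1
- true one-sided error of the unadjusted interval at the margin = 1 − Φ(1.96/k)
- unadjusted power = Φ((2.806 − 1.96)/k)
- adjusted power = Φ(2.806/k − 1.96)

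| R² | k | Excess width | True one-sided error | Half-width, unadjusted → adjusted | Power, unadjusted | Power, adjusted | Gain (points) |
|---|---|---|---|---|---|---|---|
| 0% | 1 | 0 | 2.5% | 6.98 → 6.98 | 80.1% | 80.1% | 0 |
| 5% | 0.975 | 2.6% | 2.2% | 6.98 → 6.81 | 80.7% | 82.1% | 1.4 |
| 10% | 0.949 | 5.4% | 1.9% | 6.98 → 6.63 | 81.4% | 84.1% | 2.7 |
| 20% | 0.894 | 11.8% | 1.4% | 6.98 → 6.25 | 82.8% | 88.1% | 5.3 |

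At R² = 10%, adjustment gives the precision of 63/0.9 = 70 per group.

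**What these R² values mean on the scale.** With half the women in each stratum, R² = 0.25 × gap² / 400, where gap is the planned–unplanned difference in mean tone. R² of 5%, 10% and 20% then need gaps of 8.9, 12.6 and 17.9 points. At a gap of 5 points (R² 1.6%), power is 80.3% unadjusted and 80.7% adjusted; at 10 points (R² 6.3%), 80.9% and 82.6%. With 30% unplanned, a 10-point gap gives 80.8% and 82.2%.

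**Simulation check** (20,000 runs, 64 per arm, half unplanned). At a gap of 10, power was 81.7% unadjusted and 83.3% adjusted, with one-sided error 2.0% and 2.4%. At a gap of 20, power was 83.3% and 89.8%. This agrees with the formulas.

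**The case against.** The strongest reply is that the planned analysis is valid and matches its sample size. The trial is sized on a total SD of 20 without adjustment, and an unadjusted interval delivers the promised 80% or slightly more. Any error is in the conservative direction. This stands. A reader might infer that the trial falls short of its planned power, or that a false claim of non-inferiority becomes more likely. The documents support neither.

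The size is also uncertain. The article states neither the size nor the direction of the different response. Two of the three assumed R² values imply a gap between strata larger than the 10-point margin. For gaps up to 10 points the gain is under 2 points of power. This stands, and it makes the point conditional.

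A reader might set the t-based 79.5% against adjusted powers of 81.5%, 83.5% and 87.6% and read gains of 2.0, 4.0 and 8.1 points. That comparison is not like for like, because stratified randomisation also raises the power of the unadjusted analysis once the stratum is prognostic. The gains in the table are the fair ones.

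Finally, a reader might infer that the stratum is ruled out of every model. The additional model's list is open-ended, and it includes duration of antenatal oxytocin, which partly stands in for the stratum. Fuller covariate lists for secondary models, and estimates within strata, may properly sit in a document that is not shown. None of this alters the primary interval, which the article keeps separate from the adjusted model.

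**Conclusion.** The point holds for the primary analysis as a free improvement, not as an error that endangers the conclusion. The design balances a factor that it expects to matter, and the deciding interval then makes no use of it. If planned/unplanned caesarean explains 5% to 20% of the variance in tone, the interval is 2.6% to 11.8% too wide and 1.4 to 5.3 points of power are forgone. If the strata have the same mean tone, nothing is forgone. These figures assume a true difference of 0, a total SD of 20, 63 evaluable women per group, equal SDs within strata and no interaction between treatment and stratum. For the secondary models the point is only that the stratum is not named.

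**What to change.** For both the intention-to-treat and per-protocol analyses, specify the primary analysis as a linear model of maximum uterine tone within 5 minutes on treatment and planned/unplanned caesarean. Compare the lower limit of the two-sided 95% CI for infusion minus bolus with −10; this is the same limit as that of the one-sided 97.5% interval used for the sample size. Keep the unadjusted interval as a sensitivity analysis. The same term can be added to the haemodynamic and GEE models.

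The cost is one sentence in the analysis plan and one degree of freedom. The variable is already collected, and the sample size need not change. According to the section *Randomisation and blinding*, the statistician stays blinded until the data are analysed, so the change can be fixed beforehand without knowledge of the results by arm.

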#### Definition of dataset analysed

A per-protocol and an intention-to-treat analysis will be performed, and only if both approaches support non-inferiority will the trial be considered as supporting our non-inferiority hypothesis.

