### Choice of primary endpoint

We consider the choice of the appropriate measurement of our primary endpoint as a main challenge in this trial. The choice of our primary outcome is based on a randomised controlled trial performed by Butwick et al. [11] who also used a LAS ranging from 0 to 10 to assess uterine tone in a similar setting. We expanded the scale from 0 to 100 to avoid the fact that some outcome assessors used decimal places (e.g. 7.5) while others did not. Moreover, manual palpation of the uterus represents the standard method to assess uterine tone in daily clinical practice. To reduce bias, especially when using a subjective primary outcome measurement, we have established and will maintain blinding by using a double-dummy technique for study drug administration in patients and all care providers until the statistical analysis has been performed. We have chosen to abstain from a binary assessment of the uterine tone as it would be too parallel to our secondary outcome variable ‘any additional uterotonics – yes/no’. The objective efficacy outcome of interest would have been intraoperative blood loss. Blood loss during PPH is often estimated visually, but visual assessment has been shown to be imprecise, usually underestimating blood loss particularly concerning larger volumes [21–24]. We have, therefore, decided to choose the uterine tone as our primary outcome variable. We consider blood loss as a secondary endpoint, calculated by taking into account the pre- and postoperative haematocrit and the estimated blood volume of the parturient [15].

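### The −10 verdict rests on an unadjusted CI, and the covariate model built for efficiency decides nothing: some precision may be forgone, but the test is valid

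*Protocol article*

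**What the plan says.** Under Statistical analysis plan, the protocol article answers the primary research question with "a CI of the mean difference in LAS score of the maximal uterine tone" over the first 5 minutes and compares the lower limit of that interval with −10. No covariate is named for it. The next step is the adjusted analysis: "In order to improve efficiency, an additional model will be built adjusting for the most relevant confounders". Its covariates are given as examples: obstetrician experience, either parity or the number of previous sections, a count of PPH risk factors, duration of surgery and duration of antenatal oxytocin.

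Under Definition of dataset analysed, the rule for the verdict concerns the per-protocol and intention-to-treat analyses: "only if both approaches support non-inferiority will the trial be considered as supporting our non-inferiority hypothesis". The adjusted model is not mentioned there.

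The sample size also rests on unadjusted variability: "63 patients per group are required assuming a standard deviation (SD) of 20". By contrast, the two haemodynamic endpoints are analysed by regression adjusted for baseline.

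**The concern.** The stated purpose of the adjusted model does not match its role. A narrower interval helps a non-inferiority trial only if it is the interval held against the margin. Here the wider interval decides, and the model meant to be more efficient is a side analysis.

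At stake is the chance that a truly non-inferior infusion is declared so. The plan has little slack: its sample size assumes a true difference of exactly 0, and both analysis sets must succeed. The endpoint is a subjective palpation score, so some of its variance may well be explained by characteristics known before treatment. The documents do not say how much.

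**Working it through.** **Inputs from the protocol article (Sample size justification).** One-sided 97.5 % CI, 80 % power, margin −10, SD 20, 63 per group, 10 % dropout. The true difference is not stated; 0 is assumed because it reproduces the plan's figure. R² of the covariates is not in the documents; a range of 0 to 30 % is assumed.

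**Step 1: reproduce the plan.** n per group = 2 × 20² × (1.96 + 0.8416)² / 10² = 62.8, so 63. Total 126 / 0.9 = 140. Both figures agree with the article.

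**Step 2: unadjusted power at 63 per group.** SE = 20 × √(2/63) = 3.563. CI half-width = 1.96 × 3.563 = 6.98. Power = Φ(10/3.563 − 1.96) = 80.1 %, or 79.5 % with the noncentral t distribution on 124 degrees of freedom. The planned power does not depend on adjustment.

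**Step 3: adjustment at no cost (upper bound).** Replace SD 20 by 20 × √(1 − R²). Normal approximation:

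| R² | Half-width | Power |
|---|---|---|
| 0 | 6.98 | 80.1 % |
| 5 % | 6.81 | 82.1 % |
| 10 % | 6.63 | 84.1 % |
| 20 % | 6.25 | 88.1 % |
| 30 % | 5.84 | 91.8 % |

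**Step 4: charge for estimating the covariates.** With k covariate terms and N = 126, chance imbalance inflates the variance by about 1 + k/(N − k − 3), and degrees of freedom fall to N − 2 − k. For k = 4 the factor is 1 + 4/119 = 1.034; for k = 6 it is 1 + 6/117 = 1.051. SE = 3.563 × √(1 − R²) × √factor. Noncentral t power, against 79.5 % unadjusted:

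| R² | 4 terms | 6 terms |
|---|---|---|
| 0 | 78.2 % | 77.5 % |
| 5 % | 80.2 % | 79.5 % |
| 10 % | 82.3 % | 81.6 % |
| 20 % | 86.5 % | 85.9 % |
| 30 % | 90.5 % | 90.1 % |

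The break-even R² solves (1 − R²) × factor = 1, which gives 3.3 % for 4 terms and 4.9 % for 6.

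**Step 5: slack.** If the true difference were −2, unadjusted power would be Φ(8/3.563 − 1.96) = 61 %. With R² of 10 % or 20 % the same formula, without the charge in Step 4, gives 66 % or 71 %.

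**The case against.** The strongest reply is that nothing here is wrong. In a randomised trial the unadjusted difference in means is unbiased and controls the error rate, the sample size was built on it, and an unadjusted primary analysis with an adjusted supporting one is a coherent plan. That stands, and it limits the point to efficiency.

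The gain is also uncertain. Below an R² of about 3 to 5 % adjustment costs power, and nothing in the documents supports an R² of 20 or 30 %. That stands too.

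A reader might infer two stronger claims, and the documents support neither.

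- **That the two intervals have no order, so the more favourable one could be chosen.** Accepting either interval would raise the one-sided error above 2.5 %; simulation put it at about 3.2 to 3.8 %. But the article does give an order: the unadjusted interval answers the primary question and the other model is additional. That error rate belongs to a rule the plan does not contain.
- **That the article shows ratings to differ with obstetrician experience.** Under Choice of primary endpoint it reports that "some outcome assessors used decimal places (e.g. 7.5) while others did not". This is a rounding habit on the 0–10 scale of a previous trial, and the scale was widened to 0–100 to deal with it. Experience is a plausible covariate because the score is subjective and the plan itself lists it, not because of that remark.

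Finally, the adjusted model cannot be promoted as it stands. Its list is open, offers parity or previous sections as alternatives, and omits the stratification factor. It includes duration of surgery, which runs on after study drug. Its risk-factor count includes multiple pregnancy, although only singleton pregnancies are eligible. It also includes abnormal placentation, which may be recorded after drug is given, since drug follows cord clamping and the article does not say when this item is noted. These objections stand, and the fix has to meet them.

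**Conclusion.** The point holds as lost efficiency. The verdict against −10 rests on an unadjusted interval, and the model introduced to gain efficiency has no influence on it. The unadjusted test is valid and delivers the planned power on the plan's own inputs.

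The size depends on an R² the documents do not give. Net of the cost of 4 to 6 terms, adjustment would lose about 1 to 2 power points if the covariates explain nothing, make almost no difference at 5 %, gain about 2 to 3 points at 10 %, 6 to 7 at 20 % and 11 at 30 %. All of this assumes SD 20, 63 analysed per group and a true difference of 0. The change is worth making because the downside is small and bounded, and the model is already planned.

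**What to change.** Before unblinding, state under Statistical analysis plan that the lower limit compared with −10, in both the intention-to-treat and the per-protocol analysis, is that of the arm coefficient from one linear model of maximum uterine tone. The model contains:

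- arm;
- planned or unplanned section, the stratification factor;
- obstetrician experience;
- parity;
- duration of antenatal oxytocin;
- PPH risk factors only as known before study drug, without multiple pregnancy.

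Close the list, leave out duration of surgery, and report the unadjusted CI as supportive.

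The cost is wording. Experience, parity, risk factors and type of section are already baseline variables, and antenatal oxytocin duration is already planned for the adjusted model. It uses a few degrees of freedom, risks about 2 power points at most if the covariates are uninformative, and needs a simple rule for missing covariate values. The article reports 60 % enrolment and a blinded statistician, so the change could still be made without knowledge of allocation.

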#### Inclusion criteria

Healthy women with a singleton pregnancy undergoing a planned or unplanned CS after at least 37 completed weeks of gestation under regional anaesthesia (spinal, epidural or combined spinal-epidural anaesthesia) aged older than 18 years and with signed informed consent are eligible.

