#### Study treatment in intervention and control group

After cord clamping, each patient will receive a 1-ml bolus and a short-infusion of 100 ml 0.9 % sodium chloride, one of which contains of carbetocin 100 mcg and the other of placebo (double-dummy technique). The study intervention only contains the mode of administration of carbetocin. An independent study nurse prepares the study medication (1-ml bolus and 100-ml short-infusion with or without carbetocin 100 mcg). The nurse is the only involved person with access to the randomisation results. All syringes and short-infusions will be labelled according to the Good Manufacturing Practice Guidelines with the study number (1–140) being the only differentiating feature between the study drugs.

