### Study objectives

#### Primary (efficacy) endpoint

The primary efficacy endpoint of this trial is the maximum uterine tone within the first 5 minutes after cord clamping assessed by manual palpation, and rated on a linear analogue scale (LAS) from 0 (completely atonic) to 100 (fully contracted), by the obstetrician.

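### The supporting adjusted model for uterine tone includes duration of surgery, a post-randomisation variable that can bias the treatment difference

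*Protocol article*

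**What the plan says.** Under Statistical analysis plan, the protocol article answers the primary question with an unadjusted comparison: "a CI of the mean difference in LAS score of the maximal uterine tone within the first 5 minutes after cord clamping will be calculated". It then goes further: "In order to improve efficiency, an additional model will be built adjusting for the most relevant confounders". The examples given are obstetrician experience, parity or previous caesareans, a count of risk factors for postpartum haemorrhage, and finally "duration of surgery, and duration of antenatal oxytocin infusion".

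The endpoint is defined under Primary (efficacy) endpoint as "maximum uterine tone within the first 5 minutes after cord clamping assessed by manual palpation". Treatment starts during the operation: "After cord clamping, each patient will receive a 1-ml bolus and a short-infusion of 100 ml 0.9 % sodium chloride". Randomisation and blinding places randomisation before surgery. Concomitant treatments lists six responses to inadequate tone, from massage and drugs to a balloon and surgical or radiological intervention. Definition of dataset analysed accepts non-inferiority only if the intention-to-treat and per-protocol analyses agree, and it does not mention the adjusted model.

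One smaller item sits in the same sentence. The covariate "number of risk factors for PPH (multiple pregnancy, abnormal placentation" counts multiple pregnancy, while Inclusion criteria admits "Healthy women with a singleton pregnancy undergoing a planned or unplanned CS".

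**The concern.** Covariate adjustment in a randomised trial gains precision without bias when the covariates are settled before treatment. Duration of surgery is not. It is known only when the operation ends, after the drug has been given and tone has been rated. It cannot have caused an imbalance between randomised arms, so it is not a confounder. It may also be a consequence of the outcome, because several of the listed responses to inadequate tone could plausibly prolong the operation.

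Conditioning on a consequence of the outcome changes what the treatment coefficient estimates. If the infusion truly gives lower tone, and lower tone lengthens surgery, part of the deficit is attributed to duration and the adjusted difference shrinks towards zero. For a non-inferiority claim that is the anti-conservative direction. What is at stake is the supporting analysis of the primary endpoint, which readers may take as confirmation or prefer because it is presented as the more efficient one.

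**Working it through.** **Inputs.** From Sample size justification: margin −10, SD 20, one-sided 97.5% interval, 80% power, 63 per group, 10% dropout, 140 in total. From Randomisation and blinding: 1:1 allocation. Assumed, because the article gives no figure: a within-arm correlation of −r between tone and duration, with r from 0.1 to 0.5. Duration is taken in its ordinary sense, up to the end of the operation.

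**Step 1: reproduce the plan's figure.** n = 2 × 20² × (1.960 + 0.842)² / 10² = 62.8, so 63 per group. 126 / 0.9 = 140. Both agree with the article.

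**Step 2: order of events.** Randomisation, surgery begins, cord clamping, study drug, tone rated within 5 minutes, surgery ends. Duration is complete only at the last step.

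**Step 3: effect of adjusting.** Scale duration to a within-arm SD of 1, let Δ be the true infusion-minus-bolus difference, and let arm affect duration only through tone.
- Difference in duration between arms: −rΔ/20.
- Within-arm slope of tone on duration: −20r.
- Adjusted difference: Δ − (−20r)(−rΔ/20) = Δ(1 − r²).
- Standard error: 20 × √(1 − r²) × √(2/63).
- Chance of showing non-inferiority: Φ[(Δ(1 − r²) + 10)/SE − 1.960].

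**Step 4: true difference at the margin, Δ = −10.**

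| r | Adjusted estimate | SE | One-sided error |
|---|---|---|---|
| 0 (no adjustment) | −10.0 | 3.563 | 2.5% |
| 0.1 | −9.9 | 3.546 | 2.7% |
| 0.2 | −9.6 | 3.491 | 3.3% |
| 0.3 | −9.1 | 3.399 | 4.5% |
| 0.4 | −8.4 | 3.266 | 7.1% |
| 0.5 | −7.5 | 3.086 | 12.5% |

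Worked for r = 0.3: −10 × 0.91 = −9.1; (−9.1 + 10)/3.399 = 0.265; Φ(0.265 − 1.960) = 4.5%. Simulation (6,000 trials per setting) gave errors of 3.4%, 4.8% and 12.1% at r = 0.2, 0.3 and 0.5, in line with the formula.

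**Step 5: other true differences, r = 0.3.**
- Δ = −5: estimate −4.55; chance of showing non-inferiority rises from 28.9% to 36.1%.
- Δ = 0: estimate unchanged at 0; power rises from 80.1% to 83.7% through smaller residual variance.
- Δ = +5: estimate +4.55, so a true advantage of the infusion is also shrunk.

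**Step 6: a second route from arm to duration.** If the infusion also shifts duration by d SD by a route other than tone, the adjusted difference is Δ(1 − r²) + 20rd. At Δ = −10 and r = 0.3:
- d = −0.3 (shorter surgery): −9.1 − 1.8 = −10.9; simulated error about 1.4%.
- d = +0.3 (longer surgery): −9.1 + 1.8 = −7.3 (simulated −7.4); simulated error about 11%.

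**The case against.** The strongest defence is that the trial's conclusion does not depend on this model. The unadjusted interval answers the primary question, and the decision rule names only the intention-to-treat and per-protocol analyses. That stands. A reader might infer from the table that the trial's own type I error could reach 12.5%. The article does not support that: the figure belongs to the adjusted model alone and would matter for the decision only if the adjusted result were substituted for the planned one.

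Second, the direction of bias is not fixed. A reader might infer that adjusting for duration always pulls towards non-inferiority. It does so only when the infusion is truly worse and no opposing route links arm to duration. Step 5 shows no shift at a true difference of 0, and Step 6 shows a reversal. This stands too, although a bias of unknown sign is hardly a reason to keep the covariate.

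Third, that poor tone lengthens surgery is an inference from the list of responses to inadequate tone, several of which need not prolong the operation. Total duration also includes time before clamping, which neither tone nor treatment can alter. Both points favour small r, where the effect is slight: 0.4 points and 3.3% at r = 0.2.

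Fourth, the covariates are introduced as examples, and a fuller analysis plan may exist. That leaves the list open, but duration of surgery is named in it.

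**Conclusion.** The point holds as a flaw in a pre-specified supporting analysis. Duration of surgery is mislabelled as a confounder: it is completed after randomisation, treatment and endpoint, and may be a consequence of the tone being analysed. Adjusting for it can bias the treatment coefficient instead of only improving efficiency.

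The size rests on an assumed r and on tone being the only route from arm to duration. Under those assumptions the bias at the margin runs from 0.1 to 2.5 points over r = 0.1 to 0.5, and the lower part of that range is the more plausible. The planned primary interval, the two-population rule and the sample size are untouched. Counting multiple pregnancy is an inconsistency without numerical effect, since the item is zero for every eligible woman.

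**What to change.** Delete duration of surgery from the additional model and state that its covariates are limited to variables fixed before treatment. Suitable ones are the planned/unplanned stratum already used in the randomisation, obstetrician experience, parity or number of previous caesareans, the risk-factor count, and duration of antenatal oxytocin. As a tidy-up, remove multiple pregnancy from the count.

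The cost is analysis-plan wording only; sample size, data collection and primary analysis stay as they are. Trial status reports 60% enrolment at submission, and the statistician is to stay blinded until the data are analysed, so the change can be recorded before any result by arm is known.
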